9.2.3 Exploratory Outcomes (to be described in separate analysis plans)

9.2.3.1 Pharmacology (see section 10.0).

9.2.3.2. Antifungal drug susceptibility of cryptococcal isolates.

9.2.3.3 Ability of LFCrAg assay to detect cryptococcal antigen in stored urine, serum, plasma, and CSF.

### 9.3 Sample Size and Criteria for Stages 1 and 2

9.3.1 Stage 1

The team feels that standard dose (400 mg/day) fluconazole would have about 5% DLT as defined in this study. To avoid the toxicity and difficulty of administration of ampho B, the team feels that ≤25% DLT would be acceptable. In the international setting and in participants with HIV and AIDS, the team also has concluded that there likely will be up to a 15% very early mortality rate in any cohort due to CM and/or HIV, not to the dose of fluconazole. Including participants who received very little fluconazole in safety evaluations to determine dose escalation could bias the evaluation either to be too high (if early deaths without toxicity are considered to be DLTs) or too low (if early deaths without toxicity are included in the denominator of the DLT rate). Thus, for primary safety evaluations, very early deaths (prior to Day 4) will not be included in the decision rule whether they experienced a DLT prior to early death or not [French, 2002; Okongo, 1998; Hakim, 2000; van der Horst, 1997; Brouwer, 2004; Pappas, 2004; Bicanic, Meintjes, et al, 2008; and Milefchik, 2008]. Should more than 6 very early deaths be seen in a cohort, enrollment to the cohort will by paused while the team evaluates the events carefully in conjunction with the SMC to consider if there should be study modifications. Secondary evaluations prior to escalation will include all subjects in a failure-time analysis of DLT with early deaths censored if DLT did not occur prior to death.

The dose escalation rule to be used in Stage 1 is:

- 0-3 DLTs; escalate to the next higher dose.
- 4-9 DLTs; do not escalate. This is the MTD.
- > 9 DLTs; the prior dose is the MTD.

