Should > 9 DLTs be observed before a cohort is fully accrued, accrual to that cohort will be suspended pending review. The derivation of this rule is based on calculations for a wide range of potential evaluable sample sizes, escalation rules, and scenarios about the rates of DLT at the three fluconazole doses. The following table provides the study-wide operating characteristics of this rule for an example of DLT rates across the three doses if there are 20 or 22 subjects evaluable at each dose, where the “average” DLT was calculated as the weighted average of the underlying rates of DLT.

Table 9-1

| True DLT  1200,1600, 2000 | Prob 1200 Is  > MTD | Prob  1200 Is MTD | Prob  1600 Is MTD | Prob 2000 Is MTD | Average  DLT |
| --- | --- | --- | --- | --- | --- |
| N=20/dose |  |  |  |  |  |
| 0.05, 0.10, 0.20 | 0.000 | 0.016 | 0.139 | 0.845 | 0.184 |
| 0.10, 0.20, 0.30 | 0.000 | 0.142 | 0.542 | 0.316 | 0.217 |
| 0.20, 0.30, 0.40 | 0.010 | 0.625 | 0.338 | 0.026 | 0.237 |
| N=22/dose |  |  |  |  |  |
| 0.05, 0.10, 0.20 | 0.000 | 0.022 | 0.184 | 0.794 | 0.178 |
| 0.10, 0.20, 0.30 | 0.000 | 0.189 | 0.588 | 0.223 | 0.203 |
| 0.20, 0.30, 0.40 | 0.020 | 0.710 | 0.260 | 0.010 | 0.224 |

Thus, for example, if 22 participants are evaluable at each dose level and the underlying true DLT rates are 10, 20 and 30% at 1200, 1600, and 2000 mg doses, there is a 19% chance that 1200 mg will be found to be the MTD, a 59% chance that 1600 will be found to be the MTD, and a 22% chance that 2000 will be found to be the MTD in Stage 1. Stage 2 will provide additional information on safety that will refine these findings.

Assuming exclusion of up to 15% very early deaths from a cohort, accrual of 24 participants at each dose level will yield 20-22 evaluable participants at each fluconazole dose level. Application of the same escalation rule above regardless of the sample size within this range provides consistent escalation probabilities and adjustment to the rule to reflect the number of evaluable participants is not necessary. The dose rule also maintains an average DLT below 25% given the scenarios presented in Table 9-1 should a dose level have more (or fewer) evaluable participants than 20-22. Additionally, as noted previously, DLT will also be evaluated with all participants using a censored approach.

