To provide additional detail on this component of the study, the following tables show the within-cohort probabilities of escalation, determination that a current dose is the MTD, or that the prior dose is the MTD for N=20 or 22 evaluable participants at a dose and a range of true underlying rates of DLT.

Table 9-2

|  | .05 | .10 | .20 | .30 | .40 | .50 |
| --- | --- | --- | --- | --- | --- | --- |
|  |  |  |  |  |  |  |
| N=20 |  |  |  |  |  |  |
| Prob(Escalate) | .984 | .867 | .411 | .107 | .016 | .001 |
| Prob(this MTD) | .016 | .133 | .579 | .780 | .580 | .250 |
| Prob(prior MTD) | .000 | .000 | .010 | .113 | .404 | .748 |
|  |  |  |  |  |  |  |
| N=22 |  |  |  |  |  |  |
| Prob(Escalate) | .978 | .828 | .332 | .068 | .008 | .000 |
| Prob(this MTD) | .022 | .172 | .662 | .840 | .617 | .261 |
| Prob(prior MTD) | .000 | .000 | .006 | .092 | .376 | .738 |
|  |  |  |  |  |  |  |

Simultaneous randomization to an ampho B-based regimen during Stage 1 will provide approximately 24 concurrently treated participants for preliminary information on underlying safety, mortality, and efficacy with this arm in an international multi-center setting. This will also ensure that participants in the combined ampho B data span the time of accrual to fluconazole, and reduce bias that might occur should all participants receiving ampho B be accrued only during Stage 2 when sites and participants are aware of the general outcome of Stage 1.

The rate and nature of deaths on Stage 1 will be carefully reviewed on an on-going basis. As noted below, should more than 6 very early deaths be seen in a fluconazole cohort, the team will evaluate the events carefully in conjunction with the SMC to consider if there should be study modifications. There is a 6% chance of a review being triggered if the true early mortality rate is 15% as anticipated, a 61% chance of review if the underlying rate is 30%, and a 90% chance of a review being triggered if the underlying rate is 40%.

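### Table 9-1 and the N=20 half of Table 9-2 were computed with an upper cut of more than 8 DLTs, not the stated more than 9, so the two tables conflict at N=22

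*Protocol*

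**What the plan says.** Section 9.3.1 (Stage 1) of the protocol sets out the rule in three bands of DLT counts. A low count moves the study up a dose; a middle count halts escalation and names the current dose: "4-9 DLTs; do not escalate. This is the MTD". The top band steps back one level: "> 9 DLTs; the prior dose is the MTD". The same upper count serves as the early suspension trigger: "Should > 9 DLTs be observed before a cohort is fully accrued, accrual to that cohort will be suspended pending review".

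Table 9-1 is presented as the study-wide operating characteristics of this rule "if there are 20 or 22 subjects evaluable at each dose". The text after it says that one rule applies whatever the evaluable number in the 20-22 range. The last N=22 row reads "0.20, 0.30, 0.40 | 0.020 | 0.710 | 0.260 | 0.010 | 0.224" (true DLT rates; probability that 1200 mg is above the MTD; probabilities that 1200, 1600 and 2000 mg are the MTD; average DLT).

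Table 9-2 gives the within-cohort probabilities. Its bottom rows, for true DLT rates of .05, .10, .20, .30, .40 and .50, are:

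- N=20: "Prob(prior MTD) | .000 | .000 | .010 | .113 | .404 | .748"
- N=22: "Prob(prior MTD) | .000 | .000 | .006 | .092 | .376 | .738"

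**The concern.** Two things can be seen without recalculating the tables.

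- With a true rate of 20% at 1200 mg and 22 evaluable participants, finding 1200 mg above the MTD is the same event as Prob(prior MTD) at .20. Table 9-1 gives 0.020 and Table 9-2 gives .006.
- With a fixed count as boundary, the chance of exceeding it must rise with the number evaluable. Table 9-2 shows it falling from N=20 to N=22 at every rate where it is not zero (.010 to .006, .113 to .092, .404 to .376, .748 to .738). No single boundary can do that.

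At stake is the stated ability of the rule to reject a dose that is too toxic, given that the protocol accepts at most 25% DLT. The written rule and the rule behind most of the tables also classify a cohort with exactly 9 DLTs differently: the first calls the current dose the MTD, the second the prior dose.

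**Working it through.** **Inputs.** Escalate at 3 or fewer DLTs; evaluable n = 20 or 22; true DLT rates from the two tables (all section 9.3.1). The upper cut m is 9 under the stated rule; m = 8 was tried as the alternative.

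**Formulas.** With X binomial(n, p), at each dose:

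- escalate: a = P(X ≤ 3)
- this dose is the MTD: b = P(4 ≤ X ≤ m)
- prior dose is the MTD: c = P(X > m)

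Study-wide, with subscripts 1, 2, 3 for 1200, 1600 and 2000 mg:

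- P(1200 above MTD) = c1
- P(MTD = 1200) = b1 + a1·c2
- P(MTD = 1600) = a1·(b2 + a2·c3)
- P(MTD = 2000) = a1·a2·(a3 + b3)
- average DLT = sum of P(MTD = dose) × true rate

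**Reproducing the quoted row (N=22; 20/30/40%).**

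- m = 8: c1 = .020; b1 + a1·c2 = .648 + .332 × .186 = .710; then .260 and .010; average .224. This is the printed row.
- m = 9: c1 = .006; .662 + .332 × .092 = .692; then .288 and .014; average .230. This is not the printed row.

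**All blocks.**

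| Block | Cut that reproduces it |
| --- | --- |
| Table 9-1, N=20 (3 rows) | more than 8, within 0.001 |
| Table 9-1, N=22 (3 rows) | more than 8, within 0.001 |
| Table 9-2, N=20 | more than 8, every cell |
| Table 9-2, N=22 | more than 9 (stated), every cell |

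Chaining the printed N=20 block of Table 9-2 gives back the N=20 rows of Table 9-1. Chaining the printed N=22 block gives .006/.693/.287/.014 for the 20/30/40% scenario, against the printed 0.020/0.710/0.260/0.010. The two tables therefore conflict only at N=22.

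**Table 9-2, N=20, under the stated rule.**

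| True DLT | This MTD: printed | stated rule | Prior MTD: printed | stated rule |
| --- | --- | --- | --- | --- |
| .20 | .579 | .586 | .010 | .003 |
| .30 | .780 | .845 | .113 | .048 |
| .40 | .580 | .739 | .404 | .245 |
| .50 | .250 | .411 | .748 | .588 |

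The gap in Prob(prior MTD) is .113 − .048 = 6.5 points at 30%, .404 − .245 = 15.9 points at 40%, and .748 − .588 = 16.0 points at 50%.

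**Table 9-1 under the stated rule** (P 1200 above MTD; MTD = 1200; 1600; 2000; average DLT).

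| N | True DLT | Stated rule |
| --- | --- | --- |
| 20 | 5/10/20% | 0; .016; .133; .851; .184 |
| 20 | 10/20/30% | 0; .135; .525; .340; .220 |
| 20 | 20/30/40% | .003; .606; .358; .033; .242 |
| 22 | 5/10/20% | 0; .022; .173; .805; .179 |
| 22 | 10/20/30% | 0; .177; .573; .250; .207 |
| 22 | 20/30/40% | .006; .692; .288; .014; .230 |

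The largest shift is .288 − .260 = 2.8 points. Average DLT changes by at most .230 − .224 = .006. The worked example (N=22; 10/20/30%) goes from 19%/59%/22% to 18%/57%/25%.

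**The case against.** The best defence is that little turns on this. Whether to expose new participants to a higher dose depends only on the 0-3 boundary, which is used correctly throughout, so every Prob(Escalate) entry is right. Table 9-1 moves by under 3 points, the worked example keeps its ranking, and average DLT still stays below 25%, with a maximum of 0.242. The two cuts differ only for a cohort with exactly 9 DLTs. Section 5.1 describes Stage 1 as completed, although other passages still use the future tense. All of this stands and limits the finding.

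Three stronger readings are tempting and are not supported.

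- That both tables are wrong throughout: the N=22 block of Table 9-2 is correct for the stated rule.
- That the protocol's claim of consistency between 20 and 22 evaluable rests on mixing two rules: that claim concerns escalation probabilities, which do not depend on the upper cut, and Table 9-1 uses one cut at both sizes.
- That the error fixes the wrong Stage 2 doses: section 9.3.2 bases that choice on toxicity grades and types, dose modifications, interruptions, discontinuations, early mortality and CSF clearance as well as DLT rates, and section 9.4 adds monitoring committee review.

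The mismatch itself has no defence in the text. A boundary that varies with n is excluded by the statement that one rule applies across the range, and by Table 9-1 using more than 8 at N=22 as well. The suspension trigger uses the same count of more than 9, so it does not explain the difference either.

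**Conclusion.** The tables are wrong as written for the stated rule in three of their four blocks. The error that matters is Table 9-2 at N=20. It overstates by 6.5 points at 30% true DLT, and by about 16 points at 40% and 50%, how often the stated rule sends the MTD back to the prior dose. It correspondingly understates how often such a dose is accepted as the MTD (.739 against a printed .580 at 40%). The other errors are an internal contradiction at N=22 and shifts of under 3 points in Table 9-1 and its worked example. The result assumes independent DLTs with a common rate within a dose and exactly 20 or 22 evaluable. Those assumptions are evidently the protocol's own, since they reproduce its figures once the cut is matched. The check shows which cut produced each block; it does not show which cut was intended or which is appropriate.

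**What to change.** Reconcile the rule text and both tables to a single upper boundary, chosen by the sponsor, and state it once.

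- If more than 9 stands, replace all of Table 9-1 and the N=20 block of Table 9-2 with the stated-rule values above, and change the worked example to 18%/57%/25%. The N=22 block of Table 9-2 stays.
- If more than 8 was the boundary meant, reconcile the rule text, the suspension trigger (which uses the same count of more than 9) and the N=22 block of Table 9-2. With that cut, the N=22 values at .20/.30/.40/.50 are .648/.745/.446/.143 for this MTD and .020/.186/.546/.857 for prior MTD.

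In either case, confirm in the text that the escalation probabilities are unchanged and that average DLT stays below 25% in the tabulated scenarios. Under the first option the cost is text and table edits, with a less favourable stated chance of rejecting a toxic dose at N=20. The second also changes the written rule, so the sponsor should then check whether any Stage 1 cohort had exactly 9 DLTs. Neither option changes the sample size.

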Participants who experience a treatment limiting toxicity (TLT), defined as a toxicity to ampho B treatment that results in discontinuation of that treatment prior to day 14 and prior to receipt of a total of 8.4 mg/kg ampho B, may either remain in Step 1 and receive an alternative treatment, such as liposomal ampho B, if available, or may enter Step 2 and receive study-provided fluconazole 800 mg or the maximum locally approved daily dose.

Participants who complete Step 1 will enter Step 3 after approximately 2 weeks.

For participants in Step 2, if negative CSF culture results are obtained prior to week 10 (i.e., negative culture results are available at or before week 8 from a sample collected at least 2 weeks previously), the participant will enter Step 3 and will receive fluconazole 400 mg daily (or 600 mg daily if receiving RIF) until week 10. It is possible that participants in Step 2 will not enter Step 3.

At week 10, all participants will enter Step 4 and receive fluconazole 200 mg daily through week 24.

Stage 2 (Dose Validation)

In Stage 1, when either the MTD of fluconazole is reached or the week 10 visit for the final participant randomized to the 2000 mg/day cohort is completed, all data through week 10 on all participants will be reviewed; the protocol will be amended before Stage 2 (Dose Validation) of the study opens. In Stage 2, participants will be randomized to receive an induction treatment of either an ampho B-based regimen or one of several doses of fluconazole **or fluconazole plus 5FC** at or below the MTD identified in Stage 1 (see A5225/HiFLAC Stage 2 Flow Chart).

Stage 1 and Stage 2 Evaluations

Participants will be monitored for safety and toxicity throughout the study period.

The primary efficacy outcome measure is the change in quantitative CSF culture for Cryptococcus at week 2. At screening or entry and again at week 2, CSF samples for culture will be collected from all participants. Additional CSF samples will be collected and cultured from participants on study treatment at weeks 4, 6, 8, and 10, as necessary until a negative culture is obtained. Treatment failure for any participant is defined as a positive culture from a CSF sample collected at week 10 and that is read by or at week 12.

Pharmacokinetic (PK) samples will be obtained at specified time points from all participants enrolled in fluconazole induction cohorts (see section 10.0 for sampling information).

DURATION 24 weeks

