**Ampho B plus flucytosine**

**The World Health Organization has made the following recommendations with respect to treatment of cryptococcal meningitis in persons with HIV infection [WHO Rapid Advice, December 2011]**

- **For the 2-week induction treatment phase, a regimen containing ampho B combined with flucytosine or fluconazole is the recommended option.**
- **In settings where ampho B is not available, regimens containing fluconazole combined with flucytosine, or high-dose fluconazole monotherapy are alternative options.**
- **For the 8-week consolidation treatment phase, a regimen containing oral fluconazole is the recommended option.**
- **For the maintenance treatment phase, a regimen containing oral fluconazole is the recommended option.**

**The recommendation for use of ampho B combined with fluconazole is based upon four clinical trials in persons with AIDS-associated cryptococcal meningitis [WHO Rapid Advice December 2011, Muzoora 2012, Loyse 2012, Pappas 2009, Brouwer 2004]. In general, the frequency and character of adverse events of combination of ampho B and fluconazole was similar to those who received ampho B alone. A mortality benefit was not demonstrated in either of the two trials in which there were direct comparisons between ampho B and ampho B plus fluconazole [Pappas 2009, Brouwer 2004]. Assessment of mycological efficacy (rate of change in CSF colony counts over time) tended to favor the combination of ampho B and fluconazole.**

| **Author** | **N=** | **Mortality** | | **Early Fungicidal Activity†** | **Comment** |
| --- | --- | --- | --- | --- | --- |
| **Brouwer AE.** | **16** | **AmB Alone**  **2/16 at 2 weeks (12%)**  **3/16 at 10 weeks (19%)** | **AmB+Flu 400 mg**  **5/16 at 2 weeks (31%)**  **7/16 at 10 weeks (43%)** | **AmB = -0.31 log10/d**  **AmB+Flu = -0.39 log10/d** | **Rate of decline in CSF colony counts AmB+Flu>AmB** |
| **Muzoora CK.** | **30** |  | **5 days AmB+Flu 800 mg**  **7/30 at 2 weeks (23%)**  **8/30 at 10 weeks (28%)** | **AmB+Flu = -0.30 log10/d** | **Single arm study with short course AmB (5 days)** |
| **Loyse A.** | **~23** |  | **AmB+Flu 800 mg**  **3/22 at 2 weeks (14%)**  **7/21 at 10 weeks (33%)** | **AmB+Flu 800 mg = -0.38 log10/d** | **Random allocation to 4 treatment arms. None assigned AmB alone.** |
|  | **AmB+Flu 1200 mg**  **4/23 at 2 weeks (17%)**  **6/22 at 10 weeks (27%)** | **AmB+Flu 1200 mg =-0.35 1og10/d** |

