Stage 1 can provide preliminary guidance on efficacy for the choice of cohorts to move to Stage 2. With 20-22 subjects with evaluable quantitative culture results over time per group, a difference in mean change in Cryptococcus (expressed as log10 CFU/ml CSF/day) of about 80% of the standard deviation of the measure can be detected with 90% power using a relaxed one-sided 0.10 alpha-level test. For example, if EFA (early fungicidal activity defined as the change from day 0 to day 14) is -0.30 with a standard deviation (s.d.) of 0.15 log10 CFU/ml CSF/day, an increase in the clearance to about -0.42 can be detected.

We recognize that the many neurological complications of CM may obscure drug-related ones. We will monitor participants for unusual neurological manifestations of CM that might be attributed to fluconazole. With 20 (22) evaluable participants, there is a 64% (68%) chance of seeing at least one episode of a completely unexpected unacceptable event that has a true underlying rate of occurrence of 5%. Should we see one or more DLTs associated with cardiac toxicity at a dose level, a targeted review will be triggered. This will happen with 88% probability if the underlying rate of cardiac toxicity is 10%. Should we see 2 or 3 DLTs in 20-22 participants at a dose level, and 2 of 2 or 2-3 of 3 are associated with hepatic toxicity, a targeted review will be performed before the dose can be escalated to the next level. As noted in 9.3.2, the nature and rates of all events will be evaluated prior to accepting any dose for further testing in Stage 2.

9.3.2 Stage 2

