The decision about which doses will be chosen for testing in Stage 2 will be based on: Stage 1 toxicity including the rates of DLT and also the grades and types of toxicity, dose modifications, the duration of treatment interruptions, and the rate of permanent treatment and study discontinuations, and general consideration of efficacy including early CM mortality, CNS clearance (both the rate of clearance and the proportion who clear), and early information on the duration of remission. An additional 24 participants will be randomized to each dose of fluconazole carried into Stage 2. The Stage 2 sample size for ampho B-based regimens will depend on how many fluconazole doses were tested in Stage 1 with the intent of having a total of 48 participants treated with ampho B between the two Stages. The randomization ratio will depend on how many fluconazole doses are tested and on the target ampho B sample size in this stage.

The target sample size of a total of 48 participants on a dose of fluconazole between Stages 1 and 2, and 48 on an ampho B-based regimen is based on:

- Ensuring that the width of a 90% confidence interval (CI) for culture negativity (early discontinuation or death = fail) within a dose or within ampho B-based regimens no wider than 25%.
- Detecting a difference in EFA of about 0.10 log10 CFU/ml CSF/day (about 67% of the s.d.) between two fluconazole doses or between a dose of fluconazole and ampho B with 90% power and a 2-sided 0.05-level test.
- Detecting a 25% difference (e.g. 50% vs. 75%) in efficacy between two fluconazole doses or between a dose of fluconazole and ampho B with 90% power (one-sided alpha=.10 test).
- Having the added ability to detect unusual or unexpected events that occur at a low rate, especially in consideration of those who might not be evaluable for toxicity given very early death. For example, if an unexpected and unacceptable event occurs at a rate of 5%, there is only a 64% chance of seeing one or more rare events in 20 participants evaluable for safety and an 87% chance of seeing one or more rare events in 40 participants evaluable for safety combined over both Stages.

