### 9.5 Analysis

9.5.1 Stage 1

Dose escalation is based on DLT and the decision rules as outlined above. As noted above, between-dose comparisons to select the fluconazole dose(s) to carry forward will largely be descriptive and not formally powered as all information will be factored into this decision.

9.5.2 Stage 2

In this pilot, we intend to combine the data over both Stages for the ampho B-based cohorts and for fluconazole doses that are tested in Stage 2. As noted above, only the confidence interval around the observed DLT rate in each dose will be adjusted for the dose escalation scheme. Analyses will employ appropriate methods such as Fisher’s exact test to compare dichotomous outcomes (e.g., Grades 3 and 4 events; CSF clearance before week 10) between doses or drugs, and t-tests or Wilcoxon tests to compare continuous covariates between two groups (or ANOVA or Kruskall-Wallis tests if three groups including ampho B). In the event all three fluconazole doses are evaluated in Stage 2, tests for trend such as ANCOVA, Cochran-Armitage and Jonckheere-Terpstra tests will be performed. Survival and other measures of time-to-event from study entry will be summarized with Kaplan-Meier estimates and, where appropriate, tested with log rank tests and possibly proportional hazards regression. The duration of the initial hospitalization will need to consider the duration of hospitalization preceding study entry. The focused neurological exam will be analyzed both on an item-by-item basis and also as a summary measure using methods such as mixed models analysis of variance or GEE that accommodate missing data and changing covariates.

The content and schedule of reports to be available to the core team, the SMC, and the full team will be detailed in the Study Monitoring Plan that will be developed prior to the opening of accrual to the study.

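### The primary efficacy measure (EFA) exists only for participants alive and cultured at week 2, yet the protocol gives no rule for early deaths and powers the combined-stage EFA comparison on all 48 per arm

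*Protocol*

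**What the plan says.** The Schema states: "The primary efficacy outcome measure is the change in quantitative CSF culture for Cryptococcus at week 2". Section 9.3.1 defines EFA as "early fungicidal activity defined as the change from day 0 to day 14", so each value needs a baseline and a week-2 sample.

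Two sizing statements rest on EFA:

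- **Stage 1 (9.3.1).** "With 20-22 subjects with evaluable quantitative culture results over time per group", a difference of "about 80% of the standard deviation of the measure can be detected with 90% power using a relaxed one-sided 0.10 alpha-level test". The worked example "is -0.30 with a standard deviation (s.d.) of 0.15 log10 CFU/ml CSF/day" gives a detectable value of about -0.42.
- **Stages 1 and 2 combined (9.3.2).** With 48 participants per arm, a difference of about 0.10 log10 CFU/ml CSF/day is to be detected with 90% power at a two-sided 0.05 level. No loss is mentioned.

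The protocol does settle early deaths for two other measures. In 9.3.1, deaths before Day 4 are left out of the DLT decision rule, and a censored analysis in all participants serves as a secondary look. In 9.3.2, the first sizing bullet concerns "culture negativity (early discontinuation or death = fail"). For EFA there is no such rule. Section 9.5.2 lists only "t-tests or Wilcoxon tests to compare continuous covariates between two groups".

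On expected loss, 9.3.1 allows up to 15% mortality before Day 4 in any cohort. The table of ampho B plus fluconazole trials in 2.1.2 shows two-week mortality between 2/16 (12%) and 5/16 (31%).

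**The concern.** A difference in EFA between two arms is a comparison among those who survived to the week-2 puncture and had it done. If patients who clear slowly are also more likely to die in the first two weeks, each arm's survivors clear faster than the arm as a whole. The distortion is larger in the arm with more early deaths, so that arm's EFA is flattered. Survival analysed separately does not correct the EFA contrast itself.

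Loss may also follow tolerability. Section 6.3.22 says that participants who stop study treatment early have no further study-required cultures. Read literally, stopping before week 2 can remove the EFA value as well.

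Two things are at stake: the size of the primary efficacy contrast used under objective 1.2.2, and whether the 90% power printed in 9.3.2 is available once the protocol's own expected losses are taken out.

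**Working it through.** **1. The plan's own figures.** For two equal groups, power is approximately Φ(δ / (s.d. × √(2/n)) − z).

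- Stage 1: δ = 0.12, s.d. = 0.15, one-sided 0.10. Power is 0.894 at n = 20, 0.905 at 21 and 0.915 at 22.
- Stages 1 and 2: δ = 0.10, s.d. = 0.15, two-sided 0.05, n = 48. The standard error is 0.15 × √(2/48) = 0.0306 and power is 0.904.

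Both statements reproduce.

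**2. What loss the documents suggest.**

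- Planning value in 9.3.1: up to 15% dead before Day 4. Then 24 × 0.85 = 20.4, which is the source of the 20-22 evaluable for DLT. The same range appears in the Stage 1 EFA statement. That statement is therefore already net of very early deaths, but it leaves little room for deaths on days 4 to 14 or missed punctures.
- Two-week deaths in the 2.1.2 table: (2 + 5 + 7 + 3 + 4) / (16 + 16 + 30 + 22 + 23) = 21/107 = 19.6%. Adding the 47-patient study from Peru (13%, taken as 6/47) gives 27/154 = 17.5%. All of these are ampho B-based.
- Missing week-2 CSF for any reason in the trial shown in Table 2-3: (33 + 33) / (202 + 179) = 66/381 = 17.3%.

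**3. Power after loss, Stages 1 and 2.**

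| Loss | Evaluable per arm | Power for 0.10 | Difference detectable with 90% power |
|---|---|---|---|
| 0% | 48 | 0.90 | 0.099 |
| 15% | 48 × 0.85 ≈ 41 | 0.855 | 0.107 |
| 20% | 48 × 0.80 ≈ 38 | 0.828 | 0.112 |

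Stage 1 hardly moves: with 19 of 24 evaluable, power is 0.88.

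**4. Size of the survivor bias when true clearance is identical.** The link between clearance and death is an assumption, so two models were used, both with s.d. 0.15.

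- Logistic model: the odds of early death rise 2 to 3 times per s.d. of slower clearance.
- Probit selection model: the shift in the survivor mean is ρ × s.d. × φ(z_d) / (1 − d). Here d is the arm's loss, z_d its normal quantile, and ρ the correlation between slow clearance and early death, taken as 0.3 to 0.5. For d = 0.31 and ρ = 0.5 it is 0.5 × 0.15 × 0.353 / 0.69 = 0.038. For d = 0.12 it is 0.5 × 0.15 × 0.200 / 0.88 = 0.017. The bias is the difference, 0.021.

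| Early mortality | Logistic, odds 2 to 3 | Probit, ρ 0.3 to 0.5 |
|---|---|---|
| 25% vs 15% | 0.009 to 0.013 | 0.007 to 0.011 |
| 31% vs 12% | 0.018 to 0.024 | 0.013 to 0.021 |
| 20% vs 20% | 0 | 0 |

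Units are log10 CFU/ml/day, and every non-zero value favours the arm with more deaths. Under the probit model at 31% vs 12%, a nominal 5% test would reject about 6.6% to 9.4% of the time. A true deficit of 0.10 would appear as 0.10 − 0.024 = 0.076 at the worst value tabulated. It shrinks but does not reverse.

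**The case against.** The strongest reply is that the handling of deaths in one continuous analysis is normal material for an analysis plan, which is not shown, and that 9.5.2 lists methods only in general terms. That stands in part: the absence of a detailed rule is not in itself an error. But this protocol does fix early-death handling for DLT and for culture negativity, and 2.1.1 warns that missing CSF cultures distorted an earlier trial. The 48-per-arm EFA statement is printed here and allows for no loss, whatever the analysis plan says.

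A second reply is that the decision does not depend on EFA alone. This stands. Survival is a primary outcome (9.2.1.3). Stage 2 dose choice weighs early CM mortality together with the rate of clearance and the proportion who clear (9.3.2). Deaths in Stage 1 are reviewed as they occur. A reader might infer that the go/no-go decision rests on a number that improves as mortality worsens; these provisions do not support that.

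Third, a reader might infer that about a fifth of each arm will be lost. The protocol states no such figure. It comes from ampho B-based studies with a range of 12-31%, no two-week mortality is given for high-dose fluconazole alone, and exclusion 4.2.1 (expected survival of two weeks or less) may lower it. Equal loss of a fifth in both arms, with the same link to clearance, would produce no bias at all. Section 9.3.1 attributes very early deaths to CM and/or HIV and not to fluconazole dose, and the Ugandan dose comparison in 2.1.1 reports similar survival in its two cohorts. The 31% vs 12% contrast is 5/16 vs 2/16 (Fisher p = 0.39).

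Fourth, the bias is small against sampling error: 0.009 to 0.024 is about 0.3 to 0.7 of the standard error of 0.034 at 38 per arm. That is fair, and it is a reason for a supportive analysis and not for a new primary measure.

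**Conclusion.** The point holds in a limited form. EFA as defined is conditional on being alive and cultured at week 2, and the protocol gives no rule for deaths in that comparison although it gives one for DLT and one for culture negativity. The combined-stage EFA power of 90% assumes 48 values per arm; at the losses the documents make plausible it is about 0.83 to 0.85. The Stage 1 power statement is sound as printed.

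The bias is a possibility, not an established error. It needs unequal early loss and a link between slow clearance and early death, and the documents quantify neither. Under the assumptions above it is about 0.01 to 0.02 log10 CFU/ml/day, roughly 10% to 25% of the 0.10 target, and zero when loss is equal. Survival as a primary outcome and the use of early CM mortality in dose choice limit the consequences. A cheap safeguard for the primary efficacy contrast is still worth fixing before Stage 2 data are compared.

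**What to change.** - Keep EFA in cultured participants as the mycological estimate.
- In 9.5.2, add a supportive Wilcoxon comparison in all treated participants, with death before the week-2 culture ranked worst. Settle in advance whether those deaths are tied or ordered by day of death.
- Report deaths before the week-2 culture, and missing week-2 cultures among survivors, by arm beside every EFA estimate.
- Restate the 9.3.2 EFA power for the evaluable number: about 0.85 at 41 per arm and 0.83 at 38, instead of 0.90 at 48. For a pilot, stating this is enough. Keeping 48 evaluable would need 48/0.85 ≈ 57 or 48/0.80 = 60 enrolled per arm.

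The cost is one extra rank analysis, with a test already named in 9.5.2 and data already collected. The drawback is that deaths not due to CM dilute the rank comparison; a South African study cited in 2.1.2 attributes about half of its deaths to competing morbidities. For that reason the rank analysis accompanies EFA and does not replace it.
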